### Participant recruitment and randomization

CONSORT guidelines [25] will be followed in the design, implementation and reporting of this randomized controlled trial. The protocol of this study was reviewed, and ethical approval was granted by the institutional review board of the University of Hong Kong and the Hospital Authority Hong Kong West Cluster (IRB #UW14-142).

To be eligible to join this study, a participant should (a) be a Form-1 or Form-2 student (aged 12 to 13 years) in a participating school, (b) have unfavorable oral health behavior(s) (that is, be a student who needs intervention), and (c) have Internet access via computers or mobile devices (smart phone, iPad etc.). Unfavorable oral health behaviors are defined as “snacking twice or more a day” and/or “brushing teeth less than twice a day.” A student will be excluded if he/she (i) is unable to cooperate in the related procedures due to severe health conditions, (ii) cannot speak Cantonese or (iii) cannot read and type Chinese.

This study will be conducted in nine secondary schools; three in each of Hong Kong’s three main districts (Hong Kong Island, Kowloon and the New Territories). All schools are co-ed schools, both sexes are included, and there is a balance in sexes across groups. The three schools in each district will be randomly allocated by the drawing of lots in sealed envelopes to one of three groups: (1) HE, (2) face-to-face MI or (3) online group MI. The group allocation will be done by a researcher not involved in delivering the intervention and assessing the outcomes.

All Form-1 and Form-2 students in the participating schools will be approached. Parental written consent and student’s assent will be obtained on their participation. Eligible participants will be identified through a standardized questionnaire on students’ demographic information, current snacking and toothbrushing habits, access to the Internet and language proficiency. The recruitment process will be monitored to ensure the characteristics of participants across the three groups are balanced with regard to their socio-demographic profile (sex and parental education level) and baseline behaviors (snacking and brushing). In the three schools allocated to each intervention group, 165 participants will be recruited; 55 from each school. The total number of participants will be 495 for the whole study.

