## Discussion

To the best of our knowledge, this study is the first attempt to introduce other mode of MI delivery, besides face-to-face individual counseling, into dental interventions. It taps into an unexplored area and is likely to generate useful evidence. Since online group MI is expected to be more convenient, accessible, and time efficient, it might address the practicality issues and pave the way for the application of MI in dental practice. The inclusion of online interventions into this study is also in line with the trend of Telehealth, in which information and communication technology is incorporated into health care delivery and is transforming the practice in many areas [30].

In this trial, randomization will be carried out at school level, instead of at individual level. Students in each participating school will receive the same intervention. This is to avoid intervention contamination, which is likely to happen if students in the same school are assigned to different groups. By randomly assigning the three schools from each district into three different groups and by monitoring the recruitment process, a balance will be reached in the characteristics of participants in the different groups with regard to their sociodemographic background and baseline behaviors. Since MI can rarely be completed in a single contact, follow-up phone calls will be made after the counseling session to assist the start of changes, explore solutions to the problems encountered, promote maintenance, avoid relapse and help re-establish change. Follow-up phone calls will not, however, be made in the HE group, so that the intervention reflects precisely the prevailing health education practice. The outcomes of the interventions will be evaluated by using psychological, behavioral and clinical measures at three points of time. This will allow us to interpret the results in a more complete manner.

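### Students appear to be consented and enrolled after their school's arm is drawn, with recruitment monitored to force balance, so entry to the sample may depend on arm

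*Protocol article*

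**What the plan says.** The Discussion states that "randomization will be carried out at school level, instead of at individual level". Under Participant recruitment and randomization, the draw comes first in the description: "The three schools in each district will be randomly allocated by the drawing of lots in sealed envelopes to one of three groups". On who does it: "The group allocation will be done by a researcher not involved in delivering the intervention and assessing the outcomes".

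The same section then turns to students. "All Form-1 and Form-2 students in the participating schools will be approached", parental consent and student assent are obtained, and "Eligible participants will be identified through a standardized questionnaire". The numbers are tied to schools that already have an arm: "In the three schools allocated to each intervention group, 165 participants will be recruited; 55 from each school".

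Between screening and numbers stands the balancing rule: "The recruitment process will be monitored to ensure the characteristics of participants across the three groups are balanced". The variables named are sex, parental education level, and baseline snacking and brushing. The Discussion presents this as a mechanism working alongside the random allocation: "by monitoring the recruitment process, a balance will be reached in the characteristics of participants in the different groups".

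**The concern.** Randomising schools makes the arms comparable only if a student's entry to the sample does not depend on the arm. Two features of the text put that in doubt.

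First, consent and screening appear to follow the draw, and the offer differs by arm. Under Oral health behavioral interventions, the health education talk is given to the whole school, so a student there hears it whether or not he or she enrols. In either motivational interviewing arm, taking part means a counselling session plus five telephone calls (two follow-up and three maintenance, Table 1). If families know the arm, the reasons for consenting can differ. Eligibility rests on self-reported habits, which can also respond to what is on offer.

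Second, monitoring can ensure balance across the three groups only if it influences who is enrolled and if whoever does the monitoring knows the groups. It can act only on the four named variables. Motivation and willingness to consent are not among them, yet motivation is what the counselling is meant to change. A well-matched baseline table would then reassure readers without showing whether the recruits were comparable in other respects.

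Any resulting difference would be a bias mixed with the intervention effect, which a larger sample would not reduce.

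**Working it through.** **1. The safeguards set against the risk**

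| Safeguard in the article | What it protects | Selection after allocation? |
|---|---|---|
| Allocator independent of delivery and assessment | The draw itself | No; staff who consent and screen students are not mentioned |
| Examiner blinded to each school's group (Outcome measures) | Outcome measurement | No |
| Intention-to-treat (Statistical analysis) | Keeping those enrolled in their arm | No; it cannot alter how they came to be enrolled |
| All Form-1 and Form-2 students approached, one questionnaire, same criteria in every arm | Uniform approach and eligibility | In part; consent and the filling of 55 places remain open |
| ANCOVA and regression on sex, socioeconomic background and baseline caries experience, among others | Measured imbalance | In part; baseline snacking and brushing are not listed, and motivation is not measured |

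**2. The plan's own numbers**

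Inputs from Sample size calculation: effect 0.4 SD, significance level 5 %, power 80 %, 132 per group, 20 % attrition.

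- n per group = 2 × (z₁₋α/₂ + z₁₋β)² / 0.4².
- Two-sided α = 0.05 with 80 % power gives 99.
- α = 0.05/3 gives 131 (132.3 with the t distribution), which agrees with 132 within rounding. The split over three pairwise comparisons is inferred, not stated. α = 0.05 with 90 % power also gives 132, but the stated power is 80 %.
- 132 / (1 − 0.20) = 165 per group; 3 × 165 = 9 × 55 = 495.

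These figures are not disputed here. They supply the scale for step 4.

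**3. Is there room for choice within the 55?**

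The Background cites a survey in which 32 % did not brush twice a day and 36 % snacked twice or more. Taking these rates as an assumption for the schools:

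- Complete overlap: 36 % eligible; 55 / 0.36 ≈ 153 consenting students screened per school.
- No overlap: 32 + 36 = 68 % eligible; 55 / 0.68 ≈ 81.
- Independence: 1 − 0.68 × 0.64 = 56 % eligible; 55 / 0.565 ≈ 97.

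School size and consent rate are not given, so whether a school would have more than 55 eligible consenters is unknown.

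**4. Illustration of size (the shift is assumed, not taken from the article)**

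Let b be an unmeasured prognostic difference, in SD, between two arms' recruits.

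- Share of the target effect: 0.1 / 0.4 = 25 %; 0.2 / 0.4 = 50 %.
- With 132 per group and clustering ignored, SE = √(2/132) = 0.123. With no true effect, the false-positive rate is P(Z > z − b/SE) + P(Z < −z − b/SE), where z is the two-sided critical value.
- Power when b opposes a true 0.4 SD effect, at α = 0.05/3, is Φ((0.4 − b)/SE − 2.394).

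| b (SD) | False positive, α = 0.05 | False positive, α = 0.05/3 | Power if b opposes the effect, α = 0.05/3 |
|---|---|---|---|
| 0 | 5.0 % | 1.7 % | 80 % |
| 0.05 | 6.9 % | 2.6 % | 67 % |
| 0.10 | 12.8 % | 5.8 % | 52 % |
| 0.20 | 36.9 % | 22.1 % | 22 % |

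The table shows what would follow from a shift of each size. It does not estimate the shift or its direction.

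**The case against.** The strongest reply is that the text is being read for more than it says.

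- **Order.** No word places the draw before consent. The article may simply describe allocation first, and the sentence on 55 per school can be read as giving the number per arm. This stands to the extent that the order is implied rather than stated. Allocation first is still the natural reading of recruiting in schools that already have a group.
- **Who fills the places.** A reader might infer that staff hand-pick the 55 to hit target profiles. The article does not support that: it says recruitment is monitored, describes no surplus and reports no student being turned away. If a school yields about 55 eligible consenters, there is little to choose from. What remains is that balance is to be ensured by a means the text does not define.
- **Knowledge of the arm.** Nothing states what families or recruiters are told. The article condenses a fuller protocol, so silence on this is not evidence of arm-aware consent. The balancing rule, however, is not silence: it is a stated procedure, given twice, and balancing across groups implies that someone knows the groups.
- **Mitigation.** Criteria are the same in every arm (even health education students need Internet access and must read and type Chinese), both primary outcomes are clinical and examined blind, caries is measured as an increment, and covariate adjustment is largely planned already. All of this lowers the risk. None of it reaches unmeasured differences between those who enter each arm.
- **Motive.** With three schools per arm, wanting balance is understandable. Covariate adjustment and random selection from any surplus serve that aim without arm-dependent enrolment.

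**Conclusion.** The concern holds as a risk that the stated procedure leaves open. As written, students appear to be consented, screened and enrolled in schools whose arm is already drawn, and recruitment is monitored to produce balance on four variables. Neither school randomisation nor the listed safeguards ensure that entry to the sample is independent of arm.

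The article does not support the stronger conclusions that selection bias is certain or that it favours a particular arm. Its size cannot be derived from the article; the 25 to 50 % of the target effect, and the error rates shown, rest wholly on an assumed shift of 0.1 to 0.2 SD (the error rates also on 132 per group with clustering ignored). The conclusion rests on two readings: that allocation precedes enrolment, and that monitoring can affect who is enrolled. If the sponsor intended enrolment before the draw, the text should say so, and the balancing rule would still need to be replaced.

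This should be settled before recruitment starts, because analysis cannot fully repair it afterwards.

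**What to change.** 1. In each district, complete consent, the eligibility questionnaire and preferably the baseline examination in all three schools before the envelopes are opened. If that is not feasible, have staff unaware of the arm enrol students, using identical information for families in all arms.
2. Where more than 55 eligible students in a school consent, take 55 by random draw from the list.
3. Replace the rule that recruitment is monitored to ensure balance, in both places where it appears, with a commitment to report the numbers approached, eligible, consenting and enrolled by school and arm.
4. Add baseline snacking and brushing to the covariates in Statistical analysis, and state that parental education is part of socioeconomic background. Sex and baseline caries experience are already listed.

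The cost is mainly a re-ordering of steps already planned, and Trial status says schools are still being contacted. The downside is waiting: the first school in a district is held until the third has finished, so its baseline data are slightly older when the intervention begins.

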### Oral health behavioral interventions

In the HE group, prevailing oral health education will be delivered through a 20-minute oral health talk given by a dental hygienist to the whole school. Aided by PowerPoint presentation and mouth models, the talk will cover several topics: (a) importance of oral health and the impacts of oral diseases on one’s daily life (physical, psychological and social well-being); (b) common oral diseases (dental caries and periodontal diseases) and their causes; and (c) tips (healthy diet, toothbrushing, etc.) for protecting oral health. There will be time for students to raise questions, which will be answered by the dental hygienist.

Each participant in the “face-to-face individual MI” group will join a one-on-one MI counseling in a quiet room provided by the school. Two dental hygienists will be trained in using MI to elicit behavioral changes. The training includes both theoretical and practical sessions and will be delivered by a health psychologist who is experienced in teaching MI in a healthcare setting. A hygienist will proceed to contact participants only when he/she demonstrates satisfactory competence as evaluated by the Motivational Interviewing Treatment Integrity (MITI) scale [26]. The counseling will follow the MI spirits (collaboration, acceptance, evocation and compassion), core skills (open questions, reflection, affirmation, and summary), and processes (engaging, focusing, evoking, and planning) elaborated by the MI founders [4]. A typical MI session lasts for 20 to 30 minutes and contains the following elements: (i) the counselor begins with establishing rapport, getting the participant to talk and engaging him/her in sharing his/her own thoughts about oral health; (ii) by asking open questions, attentive listening and reflection, the counselor will bring the conversation to a more focused and deeper stage, thereby identifying the discrepancy between the participant’s present behaviors and personal goals; (iii) the counselor will try to elicit and reinforce the participant’s own talk of change (desire, ability, reason, need, commitment, action and taking steps) and affirm his/her positive intentions, personal strength, efforts etc.; and (iv) if the participant is ready to set a plan, the counselor will explore what change he/she would like and feels confident to try, discuss the barriers and risky scenarios and explore possible solutions.

For online group MI, participants who share the same unfavorable behavior(s) (that is, infrequent toothbrushing, snacking, or both) will form a group of six to eight [14] and join an online MI session led by a dental hygienist. Through an online chat room created in a secure server, the synchronous (real time) text-based online session lasts for 30 to 45 minutes and follows the MI principles and group facilitation strategies. The session starts with a simple welcome and orientation, so that members become acclimated to the group setting and have an agreement on the topics of focus for the group. During the *engagement* phase, the counselor helps members become comfortable with participating and focuses on facilitating early group process on members’ issues and concerns. As the group moves into the *exploring perspectives* phase, the counselor helps deepen members’ interactions as they explore their individual viewpoints and situations together. During the *broadening perspectives* phase, interactions continue to deepen and broaden as the counselor encourages members to consider new possibilities, to allow buried hopes to reemerge and to take others’ perspectives into consideration. During the *moving into action* phase, the counselor guides members to develop specific change plans, to delineate steps toward their goals, to identify high risk situations (for example, outings and social functions) and environmental factors (for example, the temptation of fast food and unhealthy cooking in their families), and to explore possible solutions transferable to their daily lives. To close the session, the counselor summarizes the perspectives gained (or abandoned) and the experiences shared, highlights any messages for members to take with them and links the themes back to the large process of change that members are undertaking. During the whole session, the counselor engages members as a group rather than as a collection of individuals. While maintaining an individualized, client-centered focus, the counselor remains attuned to group dynamics and builds group cohesion and momentum by linking members’ interest, perspectives, experiences and concerns. The counselor allows the group to unfold at a comfortable and unpressured pace and finds a balance between providing structure and allowing spontaneity.

The face-to-face MI session will be audiotaped, and the text conversation in the online MI groups will be downloaded. Both will be periodically reviewed, and 15 % of the sessions will be coded using MITI to assess the MI fidelity. In both of the MI groups, each participant will only join one counseling session. Two follow-up telephone calls will be made in a month after the MI session to assist the participant’s preparation for change, encourage him/her to start, and discuss difficulties and possible solutions. To maintain the behavioral change and avoid relapse, participants will be contacted through the telephone three more times up to 6 months after the initial contact [9, 10]. The timeline and purposes of the follow-up telephone calls are shown in Table 1.

**Table 1 Tab1:** Intervention activities for both motivational interviewing (MI) groups

Activity	Time	Goals
Initial counseling (X1)	Start of study	Establish rapport, discuss need and options, use strategies that structure and elicit change and set goals
Follow-up telephone calls (X2)	2 weeks and 1 month after initial counseling	Assist preparation, encourage start and solve problems
Maintenance telephone calls (X3)	2, 4 and 6 months after initial counseling	Promote maintenance, avoid relapse and help re-establish change, if needed

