### Statistical analysis

Data will be analyzed using the computer software Statistical Package for Social Sciences (SPSS). Effectiveness of the intervention schemes over 6, 12 and 24 months will be evaluated on an intention-to-treat basis. All participants randomly assigned to each group will be included in the analysis, regardless of whether they receive the intervention or complete the study. If a participant is lost to follow-up, the last known outcome status will be carried forward.

Chi-square tests will be used for comparing distributions, whereas parametric or nonparametric methods, as appropriate, will be adopted for comparing means. Effect sizes (relative risk) and their 95 % confidence intervals (95 % CI) will be calculated and reported with *P* values. Multivariate analysis, namely ANCOVA (analysis of covariance) and multiple regressions, will be performed to evaluate the effects of various factors (intervention, school, counselor, participant’s sex, socioeconomic background and baseline caries experience) on the outcomes.

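### Only the online arm is treated in small chat groups, and the stated student-level analysis omits that layer; if outcomes correlate within chat groups, standard errors for comparisons with the online arm are understated

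*Protocol article*

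**What the plan says.** Under Oral health behavioral interventions, the Protocol article has online participants sorted by their unfavorable behavior (brushing, snacking or both). They then "will form a group of six to eight" and attend one real-time text session, in which "the counselor engages members as a group rather than as a collection of individuals".

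The comparators differ in structure. Each face-to-face participant "will join a one-on-one MI counseling in a quiet room". Health education is a talk "given by a dental hygienist to the whole school". Neither has a small treatment group between student and school.

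The Statistical analysis section plans chi-square tests for distributions and parametric or nonparametric comparisons of means. It adds multivariable models, "namely ANCOVA (analysis of covariance) and multiple regressions", on these factors: "intervention, school, counselor, participant’s sex, socioeconomic background and baseline caries experience". Chat group is not listed. No random effect, cluster-robust error or school-level analysis is stated. According to Participant recruitment and randomization and the Discussion, schools are the randomized units: nine in all, three per arm, with 55 participants from each.

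**The concern.** Members of a chat group share a session, a facilitator and each other's contributions, and the intervention is designed to work through that interaction. If this leaves their outcomes more alike than those of other students in the same school, the mean of the online arm is less precise than 165 independent students would make it. The other two arms carry no such penalty, so the design is partially nested.

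The listed counselor factor does not stand in for chat group, because two hygienists lead all the groups. Student-level tests treat chat-mates as independent. Two of the three pairwise comparisons, both involving the trial's new mode of delivery, could then be tested at a higher real error rate than HE versus face-to-face, although the plan presents all three alike.

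**Working it through.** **Inputs from the article.** Chat groups of 6 to 8 (midpoint 7); 165 recruited and 132 required per arm; three schools per arm; 5% significance level. Two-sided testing is assumed because the article does not say. All randomized participants are to be analysed, with the last value carried forward.

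**Assumed.** Chat-group ICC of 0 to 0.10; the article gives none.

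**The plan's own figure.** For an effect size of 0.4 and 80% power at two-sided 5%, the normal formula gives 2 × (1.960 + 0.842)² / 0.4² = 98.1, so 99 per arm rather than 132. About 132 results from a 0.05/3 level (131 by the normal formula, 132.3 by the t-test), or from 90% power at 5% (132). The article states neither. 132 / 0.8 = 165 is exact. None of these routes contains an allowance for chat group or school.

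**Number of chat groups.** 165/8 = 20.6 and 165/6 = 27.5, so 21 to 27 groups if each has six to eight members.

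**Formulas.** With m analysed members per chat group:
- design effect in the online arm: DE = 1 + (m − 1) × ICC
- true over computed standard error against an arm without chat groups: R = √((1 + DE)/2)
- real two-sided error at nominal 5%: 2 × (1 − Φ(1.96/R))

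At ICC 0.05 and m = 7: DE = 1 + 6 × 0.05 = 1.30; R = √(2.30/2) = 1.072; 1.96/1.072 = 1.83; error 6.8%.

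| ICC | DE (m = 7) | R | Real error | Real error if m = 5.6 |
|---|---|---|---|---|
| 0 | 1.00 | 1.000 | 5.0% | 5.0% |
| 0.01 | 1.06 | 1.015 | 5.3% | – |
| 0.02 | 1.12 | 1.030 | 5.7% | 5.5% |
| 0.05 | 1.30 | 1.072 | 6.8% | 6.3% |
| 0.10 | 1.60 | 1.140 | 8.6% | 7.7% |

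m = 7 applies if all 165 are kept by carrying values forward. m = 7 × 0.8 = 5.6 applies if 20% drop out and only the 132 are analysed. For ICC 0.02, 0.05 and 0.10, the online arm's effective size is 165/DE = 147, 127 and 103 in the first case. In the second, DE is 1.092, 1.23 and 1.46, and 132/DE = 121, 107 and 90. With all 165 kept and ICC 0.05, group sizes of 6 and 8 move the error only from 6.5% to 7.1%.

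**Does the listed school factor help?** A null simulation used three schools per arm and seven chat groups of seven per online school, with 6,000 runs per setting. For online versus HE with no school effect:

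| Chat-group ICC | Student-level t-test | Within-school residual error | School means |
|---|---|---|---|
| 0.05 | 7.1% | 7.1% | 5.1 to 5.3% |
| 0.10 | 8.4% | 8.4% | 5.4 to 5.9% |

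School as a fixed factor is nested in arm, so its effects overlap completely with intervention and the error still comes from students within schools. School means absorb nearly all of the chat-group variance. The upper figures come from pooling the variance over all three arms, where the two arms without chat groups pull it down.

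**School clustering for scale.** With 132/3 = 44 students per school, a school ICC of 0.01 gives DE = 1 + 43 × 0.01 = 1.43 and a real error of about 10%; 0.02 gives DE 1.86 and about 15%. Both are without any chat-group effect, and the school ICCs are also assumptions. In the simulation, a school ICC of 0.02 with chat-group ICC 0.05 raised the student-level error from 15.4% to 17.6%.

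**The case against.** **The ICC may be close to zero.** There is one session of 30 to 45 minutes, followed by five telephone calls to each participant. The primary outcomes are new carious surfaces and gingival bleeding, followed to 24 months. A lasting chat-group effect on these could be small, and nothing in the article argues for 0.10. This stands, and the point is therefore conditional. A reader might infer that the errors are certainly too small; without an ICC the documents do not support that.

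**Chat group is a sub-point of school.** If the error came from schools and chat groups lay within schools, little would remain. This is right as to priority, but it describes an analysis that the article does not state.

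**An article may leave random effects to the full plan.** That protects silence. Here the student-level methods and a list of factors are stated, including two delivery-related factors, school and counselor. Following them as written gives the result above.

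**Three further inferences go too far.**
- That the plan favours the online arm: understated errors raise false positives equally in both directions.
- That chat groups cross schools: the article is silent. It is only a reason to state the rule.
- That sorting by baseline behavior is itself the problem: sorting makes chat-mates alike without increasing the variance of the arm mean. The concern rests on the shared session.

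**Conclusion.** The point holds conditionally. For any positive chat-group ICC, the stated student-level analyses understate the standard errors of online versus HE and online versus face-to-face. Over the assumed range the real error of a nominal 5% test runs from 5.0% to 8.6% with seven analysed per group, or to 7.7% if attrition leaves about 5.6. At an ICC of 0.01 the effect is slight. HE versus face-to-face is unaffected by this layer.

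The conclusion rests on equal arm sizes, two-sided tests and an ICC range that the documents do not supply. It is a correction of moderate size. School clustering, which affects all three comparisons, is separate and larger, and a chat-group term alone would leave that problem in place.

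**What to change.** 1. Record a chat-group identifier for every online participant. Transcripts are already to be downloaded and Trial status says that recruitment has not begun, so this costs almost nothing now.
2. Form each chat group within one school, and say so.
3. Take the error for intervention comparisons from the randomized unit. Either fit school as a random effect with small-sample degrees of freedom (for example Satterthwaite), or analyse school means, which absorb chat-group variance when chat groups lie within schools.
4. In student-level mixed models, add a chat-group random effect in the online arm only, nested in school. Include baseline snacking and brushing as covariates, so that similarity due to sorting is not counted as group variance. The listed factors do not include these two.

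**Cost.** One recorded variable and a few sentences. The chat-group layer itself widens online-arm intervals by a factor of 1.03 to 1.14 at ICC 0.02 to 0.10 (m = 7). The school level costs more: nine schools in three arms leave 9 − 3 = 6 degrees of freedom, and fewer if district is fitted. That follows from randomizing schools, and leaving school out of the error would only hide it.
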